# Effectiveness of a school-based intervention using alternative sports to improve physical and motor skills in elementary school students (RENUÉVATE Project): study protocol for a randomized controlled trial

**DOI:** 10.3389/fpubh.2026.1817081

**Published:** 2026-05-21

**Keywords:** physical education and training, schools, motor skills, exercise, teaching, child

## Abstract

**Background:**

Physical inactivity and low enjoyment of physical education during childhood represent a significant public health problem. Although schools are a key setting for promoting active lifestyles, physical education instruction continues to focus largely on traditional sports, which may limit student participation and engagement. In this context, alternative sports emerge as an innovative and potentially more inclusive pedagogical strategy. Therefore, the objective of this study is to evaluate the effectiveness of an alternative sports intervention in the school setting, compared to standard physical education, on physical fitness, body composition, motor competence, and enjoyment of physical activity among elementary school students.

**Methods:**

A cluster-randomized controlled trial will be conducted among 11- to 12-year-old schoolchildren. Schools will be selected at random, and within each school, two classes from the same grade will be assigned to the intervention or control groups. The intervention will consist of an eight-week instructional unit (16 sessions) based on four alternative sports (flag football, ultimate frisbee, korfball, and kin-ball) taught using the Teaching Games for Understanding approach. The control group will continue with the regular physical education curriculum. Physical fitness, motor competence, and enjoyment of physical activity will be assessed as primary outcomes, while physical activity levels and body composition will be considered secondary outcomes. All variables will be assessed before and after the intervention. Primary analyses will follow the intention-to-treat principle using mixed-effects models to account for clustering (students within schools). The effects of the intervention will be estimated using the group × time interaction. Analyses will be performed using SPSS v28 and R v4.3.

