**Figure 2 fig2:**
[figure not shown]
Study flowchart. P: Public administration; PS: Subsidized private administration; PU: Unsubsidized private administration.

Although body composition is not the primary outcome, it was selected as the reference variable for sample size calculation due to its high sensitivity and the existence of well-established thresholds of clinical relevance in the academic literature (26, 27). As it is a variable with greater inter-subject variability in short- to medium-term interventions, the sample size derived from it acts as a conservative estimate. This approach ensures robust statistical power (>80%) to detect significant effects not only in body composition but also in secondary variables with lower sample size requirements, such as motor competence or enjoyment (28).

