##### Motor competence

3.9.1.1

Motor competence will be the primary outcome of the study and will be assessed using the MOBAK 5–6 (Motorische Basiskompetenzen) battery, validated for fifth- and sixth-grade elementary school children (38). This instrument assesses basic motor competence across two dimensions: self-movement (balance, rolling, jumping, and moving) and object movement (throwing, catching, bouncing, and dribbling).

Each dimension includes four motor tasks, which are scored dichotomously (0 = task not achieved; 1 = task achieved according to established criteria). Scores for each dimension range from 0 to 4 points, and the total score ranges from 0 to 8 points, with higher values indicating a higher level of motor competence.

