#### Effect estimates and statistical inference

3.13.4

Results will be presented as adjusted between-group differences in change, with corresponding 95% confidence intervals (CI). Statistical significance will be set at *p* < 0.05 (two-sided). Standardized effect sizes will be calculated using Cohen’s d, based on adjusted estimates derived from mixed-effects models, to facilitate interpretation of the magnitude of the intervention effects.

All statistical analyses will be performed using SPSS version 28.0 (IBM Corp., Armonk, NY, USA) and R version 4.3, employing the lme4 package for mixed-effects modeling and the GGIR package for processing physical activity data derived from the accelerometer.

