Similarly, the organization of sessions prioritizes a high volume of motor practice, which can translate into a greater effective physical activity load during class time. The inclusion of objective measures of physical activity using accelerometry will allow for the description and monitoring of the actual dose of the intervention, which will strengthen the interpretation of results in relation to the intensity achieved. From a motor development perspective, the selected alternative sports are characterized by requiring a wide range of motor skills, such as throwing, catching, multidirectional locomotion, jumping, and hand-eye coordination, within dynamic and constantly changing game contexts. These demands may contribute to improvements in general motor competence, a key aspect during the final stage of elementary school that is closely associated with future adherence to physical activity (56, 57). Systematic exposure to diverse, non-stereotypical motor tasks could particularly benefit students with limited experience in traditional sports, reducing barriers to participation and fostering more inclusive learning trajectories.

On an affective and motivational level, the intervention is grounded in the novelty, cooperation, and inclusivity inherent in sports such as kin-ball and korfball. These sports promote adapted rules, equitable participation, and collective goals, which can foster a task-oriented motivational climate, increasing enjoyment and intrinsic motivation toward physical activity (56, 58). Enjoyment of physical activity is a key determinant of sustained participation over time, and its assessment as a primary outcome in this protocol reflects the need to consider not only how much students move, but also how they experience motor participation in physical education classes.

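### The protocol contradicts itself on the primary outcome: three domains in the Abstract, motor competence alone in Section 3.9, so it does not settle which result decides effectiveness

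*Protocol article*

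**What the plan says.** Four places in the Protocol article assign ranks to the outcomes.

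- **Abstract, Methods.** Three domains are primary: "Physical fitness, motor competence, and enjoyment of physical activity will be assessed as primary outcomes". The sentence then gives the rest a lower rank: "while physical activity levels and body composition will be considered secondary outcomes".
- **Section 3.9.1.1 (Motor competence), under the singular heading Primary outcome.** "Motor competence will be the primary outcome of the study and will be assessed using the MOBAK 5–6". Physical fitness (3.9.2.1) and enjoyment (3.9.2.5) both stand under Section 3.9.2, Secondary outcomes.
- **Discussion (Section 4).** On enjoyment, the text refers to "its assessment as a primary outcome in this protocol".
- **Section 3.2 (Sample size, text after Figure 2).** The trial is sized on body fat percentage, which the section says is not primary. It then claims adequate power for "secondary variables with lower sample size requirements, such as motor competence or enjoyment".

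Section 3.13.2 applies one modelling approach, with the group × time interaction as the effect, to motor skills, fitness, enjoyment, physical activity and body composition alike. Section 3.13.4 sets a single two-sided threshold of p < 0.05 for the results as a whole.

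**The concern.** A protocol fixes in advance which result answers the trial's question. Here motor competence is primary in two places and secondary in a third. Enjoyment is primary in two places and secondary in two. Fitness is primary in one and secondary in another. These statements cannot all hold, and all of them are in the current text.

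Once results are known, a favourable finding on motor competence, on enjoyment or on any fitness test could be presented as a primary result with a correct citation to this article. A reader of the final report could not tell whether the headline outcome was chosen before or after the data were seen. The shared model and shared threshold do nothing to separate a deciding test from a supportive one.

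**Working it through.** **1. Rank of each outcome by place**

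| Outcome | Abstract | Section 3.2 | Section 3.9 | Discussion |
|---|---|---|---|---|
| Motor competence | primary | secondary | primary (sole) | – |
| Enjoyment | primary | secondary | secondary | primary |
| Physical fitness | primary | – | secondary | – |
| Physical activity | secondary | – | secondary | – |
| Body composition | secondary | not primary; sizing variable | secondary | – |

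There are two basic definitions: the Abstract's three domains and Section 3.9's single domain. The Discussion repeats the Abstract's view of enjoyment. Section 3.2 fits neither definition.

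**2. The plan's own sample size, reproduced**

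Inputs from Section 3.2: difference 3, SD 5, two-sided α 0.05, power 80%, class size 35, ICC 0.03, dropout 15%.

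- Unadjusted: n = 2 × [5 × (1.960 + 0.842) / 3]² = 43.6, so 44 per group.
- Design effect: 1 + (35 − 1) × 0.03 = 2.02. Then 43.6 × 2.02 = 88.1.
- Dropout: 88.1 / 0.85 = 103.6, so 104 per group.

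The stated 44, 88 and 104 all reproduce. The calculation uses one test at 0.05, on a variable that neither definition makes primary.

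**3. Error if any one primary success counts**

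For k independent tests at 0.05, family-wise error = 1 − 0.95^k.

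- Section 3.9 read as one test: 5%.
- Abstract with one test per domain, k = 3: 1 − 0.857 = 14.3%.
- Abstract with fitness as its three tests in Section 3.9.2.1 (6-min walk, long jump, handgrip) plus motor competence and enjoyment, k = 5: 1 − 0.774 = 22.6%.

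The outcomes are measured on the same children, so the tests will be correlated. The document gives no correlations. Simulating equally correlated normal test statistics at assumed values gives:

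| Assumed correlation | k = 3 | k = 5 |
|---|---|---|
| 0 | 14.3% | 22.6% |
| 0.3 | 13.6% | 20.9% |
| 0.5 | 12.6% | 18.3% |
| 0.8 | 9.8% | 12.8% |

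**4. Consequence for power**

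- *All must succeed.* Error stays at or below 5%. If each test had 80% power and the tests were independent, joint power would be 0.80³ = 51% for three and 0.80⁵ = 33% for five. Positive correlation would raise these figures.
- *Any one may succeed, with Bonferroni.* The levels are 0.05/3 = 0.0167 and 0.05/5 = 0.01. As an illustration, take the plan's standardised effect of 3/5 = 0.6 and its own method. For k = 3, 59 × 2.02 / 0.85 gives about 140 per group. For k = 5, 65 × 2.02 / 0.85 gives about 154. With 105 enrolled per group, power is 80.5% at 0.05, about 66% at 0.0167 and about 60% at 0.01.

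These power figures carry over the plan's own approximation and show only the relative cost of each rule.

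**The case against.** The strongest defence is that the operative outcome section is clear. Section 3.9.1 has a singular heading and names one domain, so the Abstract, the Discussion and Section 3.2 could be read as loose drafting. In Section 3.2, secondary may mean only secondary to the sizing variable. A multiplicity method or testing order is commonly left to a statistical analysis plan, which is not shown, and the registry entry may already fix one outcome.

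Part of this stands, and it rules out several stronger readings that a reader might infer.

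- *Three rival definitions.* The Discussion calls enjoyment a primary outcome, not the only one, which agrees with the Abstract. There are two definitions and one further conflict in Section 3.2.
- *Co-primary outcomes with inflated error.* The document does not use that term and gives no success rule. Inflation needs an any-one-success rule; if all had to succeed, the cost would be power.
- *A 22.6% error rate.* That figure also needs independence and fitness counted as three tests.
- *No controlled primary test at all.* Under Section 3.9.1 alone there could be one test at 0.05. The difficulty is that the rest of the article contradicts that section.
- *Missing multiplicity adjustment as a fault in itself.* It could sit in the analysis plan.
- *A registry mismatch.* The entry is not available here, so none can be claimed.

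What the defence does not remove is the contradiction. An analysis plan could choose one version, but this published text would still support the other. The Abstract is also too explicit to be a slip, since it ranks the remaining outcomes as secondary in the same sentence.

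**Conclusion.** The protocol gives two incompatible definitions of the primary outcome, and a third passage fits neither. With a common model and a single 0.05 threshold, it does not settle which result decides effectiveness. This rests on the text alone and needs no assumption.

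The size is conditional. If any one of the Abstract's primary outcomes sufficed, family-wise error would be about 10–14% for three tests or 13–23% for five, over assumed correlations from 0.8 down to 0. That is roughly two to four and a half times the 5% of a single test. If all had to succeed, the loss would be in power. Nothing in the documents shows which rule is intended, or that selective reporting is planned.

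**What to change.** Before outcome data are seen, name one primary outcome and use it consistently in the Abstract, Section 3.2, Section 3.9 and the Discussion.

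- **Preferred, because the most specific text already supports it:** motor competence. Section 3.9.1.1 describes two dimension scores (0–4 each) and a total (0–8) without saying which is the endpoint, so state that it is the MOBAK total. Analyse it as the between-group difference in change (group × time), as in Sections 3.13.2 and 3.13.4, at two-sided 0.05. List fitness, enjoyment, physical activity and body composition as secondary and supportive, reported with estimates and confidence intervals.
- **Alternative:** keep the three domains as primary, name the test or score for each, and state the success or multiplicity rule. The sample size would then have to match that rule.

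In either case, check that the registry entry agrees.

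The first option costs wording changes in a few places and one registry check; design and data collection are untouched. Claims on fitness and enjoyment become supportive only. Section 3.2 should also acknowledge that the sample size was calculated on body fat percentage, so the primary outcome has no calculation of its own. The second option costs more: on the illustrative Bonferroni figures, about 140 to 154 per group instead of 105, or accepting lower power.

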**Discussion:**

This protocol addresses significant gaps in the literature on school-based interventions using alternative sports. It is expected that the experimental design, together with a structured intervention that can be replicated by teachers, will generate robust evidence on the physical, motor, and affective-motivational mechanisms associated with this pedagogical approach. The anticipated findings may serve as a basis for future curricular decisions and educational policies aimed at promoting physical activity and health during school-age years.

**Clinical trial registration:**

ClinicalTrials.gov, identifier NCT07313267.

## Introduction

1

Along with body composition, physical fitness and motor competence in childhood are increasingly recognized as key indicators of health and important determinants of current and future physical activity (1, 2). Higher levels of physical fitness and better motor skills during childhood have been associated with better functional performance and greater participation in sports (3), as well as with more favorable health trajectories in later life (4). Late childhood (approximately ages 8–13) represents a particularly important period for consolidating fundamental motor skills and sport-related skills (5, 6), developing positive attitudes toward movement, and shaping sustained physical activity behaviors (7).

In the field of physical education, sport-based approaches constitute one of the most widely implemented pedagogical strategies for promoting physical activity, motor development, and social interaction in childhood (8). Sports offer structured and regulated environments that promote systematic motor practice, decision-making, and active participation, fundamental pillars for motor learning and the improvement of physical fitness (9). However, both the nature of the sport and the pedagogical model adopted significantly influence students’ levels of adherence and the effectiveness of learning outcomes (10).

In Chile, the school environment offers a strategic opportunity to promote physical activity and motor development on a large scale. Physical education, as part of the national educational framework, plays a fundamental role in students’ holistic development and in fostering active lifestyles, leadership, and self-care (11). However, participation in organized sports and extracurricular physical activities is not distributed equitably (12). Economic, cultural, and logistical barriers can limit access and sustained participation, particularly among children who do not identify with traditional sports models or who perceive themselves as less competent. Therefore, school-based approaches that prioritize participation, enjoyment, and inclusion can help reduce inequalities in physical activity opportunities.

Traditional sports in physical education typically include widely institutionalized activities, such as soccer, basketball, and handball, which are often characterized by a strong emphasis on technical performance, competition, and early specialization (13).

While these sports can be effective, they may also inadvertently limit the participation of students with perceived lower competence or little prior experience (13). In contrast, alternative sports are defined as non-traditional, adaptable, and often less institutionalized physical activities that prioritize inclusion, cooperation, and diverse motor experiences (14). These sports typically involve modified rules, mixed-gender participation, and a reduced emphasis on competition, which can foster a more inclusive and motivating learning environment (15). These practices promote students’ holistic development, increase motivation and participation in physical education classes (16), and foster equity, cooperation, and decision-making (16, 17).

It is important to note that alternative sports can also reduce structural and economic barriers, as they often require minimal specialized infrastructure and can be adapted to available school resources. This flexibility can facilitate broader implementation across diverse educational contexts, particularly in resource-limited settings, promoting students’ holistic development and fostering equity and cooperation among students (16, 17).

From a physiological perspective, participation in alternative sports can contribute to improvements in body composition through increased engagement in moderate-to-vigorous physical activity (18), higher participation rates, and a reduction in sedentary behavior during school hours (19). These factors are known to influence energy expenditure and can lead to favorable changes in fat mass and lean mass over time (20).

As for evidence regarding physical fitness and motor skills, this is much more limited and comes primarily from a few interventions focused on a single sport. Improvements have been reported in strength and power in disciplines such as padel (21) and street workout (18), in broader components of physical fitness such as endurance, strength, and speed through kin-ball (22); and, in some cases, improvements in motor skills compared to traditional physical education programs (23). However, there remains a lack of high-quality studies to determine the effects of systematic alternative sports programs implemented in schools on physical fitness, motor competence, and enjoyment among elementary school children. The RENUÉVATE project was designed to address this gap in the evidence.

Our hypothesis is that participants assigned to the intervention will show greater improvements than controls in key components of physical fitness (e.g., muscle strength, speed, and cardiorespiratory endurance), body composition (fat mass and fat-free mass), motor competence (including body and object control), and enjoyment of physical activity. Using a randomized controlled trial design and a comprehensive set of outcomes, RENUÉVATE will provide robust evidence on whether alternative sports can serve as an inclusive and engaging strategy within the school setting to promote physical and motor development, with potential implications for educational practice and early health promotion.

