## Objective

2

The aim of this study is to evaluate the effectiveness of an alternative sports program in a school setting, compared to standard physical education, on physical fitness, body composition, motor skills, and enjoyment of physical activity among elementary school students aged 11–12.

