#### Control group (CG)

3.7.2

The CG will participate only in the baseline and post-intervention assessments, maintaining its regular physical education curriculum led by its regular teacher, with no changes to the existing lesson plans or teaching methodology. The sessions will be governed by the National Curriculum Standards currently in effect in Chile, specifically in the development of Unit 2: Individual and Team Games and Sports (11).

The curriculum offered in the CG will include traditional sports (i.e., basketball, soccer, and handball) using a traditional technical-pedagogical approach, characterized by an emphasis on the acquisition of fine motor skills and basic tactical patterns. Lessons will predominantly employ direct instruction strategies (command style), based on teacher demonstration, repetitive practice of tasks (drills), and prescriptive corrective feedback. Equivalence in activity volume (frequency and duration of sessions) between the IG and the CG will be ensured to guarantee group comparability.

It should be noted that the design of this study does not aim to contrast ‘effective’ teaching with ‘ineffective’ teaching. On the contrary, it is recognized that well-structured traditional Physical Education can promote motor learning through skill progression (36). Therefore, the objective of this comparison is to determine whether a comprehensive teaching model (TGfU) integrated with alternative sports provides incremental or superior benefits in motor competence and health compared to the standard pedagogical practice (usual care) of the educational system (37).

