##### Main part (65 min)

3.7.3.2

This phase will focus on practicing the alternative sport through modified game situations and technical-tactical progressions, in line with the TGfU approach. Tasks will be designed to promote decision-making, game understanding, and motor execution, maintaining a moderate to vigorous intensity (65–80% of HRmax; RPE 12–15) (4).

Active recovery periods will be incorporated between activities to promote recovery and continuity of practice. To validate the intensity achieved, wrist-based heart rate monitors will be used on a subsample comprising 25% of the participants.

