##### Physical activity level (target)

3.9.2.3

Physical activity levels will be objectively assessed using triaxial accelerometry (ActiGraph wGT3X-BT, Pensacola, FL, USA) (43). Following the RENUÉVATE Specific Monitoring Protocol, the devices will be placed on the right hip using an adjustable elastic belt, ensuring their stability during multidirectional movements.

In accordance with the study’s central objective, to evaluate the pedagogical efficacy of alternative sports, the accelerometers will be used exclusively during Physical Education sessions (90 min). The research team will personally supervise the placement at the start and removal at the end of each class during the 8-week intervention. This methodological decision allows for rigorous control of the physical activity dose strictly linked to the pedagogical model (TGfU vs. Traditional), minimizing statistical noise from extracurricular activities.

The devices will be configured with a sampling rate of 30 Hz, and data will be processed in 15-s epochs, optimizing the capture of the intermittent nature of children’s movement (44). Non-use time will be defined as ≥20 consecutive minutes of zero counts. To ensure data validity, a session will be considered valid if it records at least 80% of the total class time, thereby ensuring an accurate representation of motor behavior during the intervention.

The intensity of physical activity will be categorized using the intensity thresholds (cut-off points) validated by Evenson et al. (45) for the pediatric population, due to their high accuracy in classifying activity levels in school settings. Data will be classified according to the following counts per minute (cpm) ranges: Sedentary: 0–100 cpm; Light physical activity (LPA): 101–2,295 cpm; Moderate physical activity (MPA): 2296–4,011 cpm; Vigorous physical activity (VPA): ≥4,012 cpm.

The primary movement variable, moderate-to-vigorous physical activity (MVPA), will be obtained by summing the time recorded in the moderate and vigorous categories. This indicator will allow us to quantify compliance with international health recommendations and determine the actual impact of the pedagogical model on students’ energy expenditure during class.

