It is important to note that, if the intervention proves effective, the RENUÉVATE project could contribute to decision-making in education and public health by supporting the incorporation of alternative sports as a valid strategy for improving physical fitness, motor skills, and enjoyment of physical activity during school-age years. Furthermore, the protocol can serve as a model for future school-based interventions aimed at promoting active lifestyles in an inclusive, sustainable, and pedagogically coherent manner.

From a public health perspective, this study is particularly relevant, as it evaluates a scalable, school-based intervention that can be integrated into existing educational systems without requiring substantial additional resources. By leveraging physical education as a universal platform, the RENUÉVATE program has the potential to reach large populations of children and contribute to early prevention strategies targeting physical inactivity, motor delays, and associated health risks. This aligns with global public health priorities focused on promoting active lifestyles from an early age.

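### The trial can estimate the effect of the RENUÉVATE package against usual physical education, but several sections credit the result to the sports alone or to the teaching model alone

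*Protocol article*

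**What the plan says.** **What the arms receive.** Sections 3.7.1 and 3.7.3 give the intervention group flag football, ultimate frisbee, korfball and kin-ball, taught by TGfU. Each session phase has an intensity range; the main part is described as "maintaining a moderate to vigorous intensity", set at 65–80% of HRmax and RPE 12–15. Section 3.7.2 gives the control group basketball, soccer and handball, and states: "Lessons will predominantly employ direct instruction strategies (command style)". It sets no intensity range for that group. It equalises session frequency and duration, and nothing else.

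**Who teaches.** Sections 3.3 and 3.7.1 assign the intervention sessions to an external, trained person, while the control classes keep their regular teacher. Section 3.8 instead has a physical education teacher receive 45–60 minutes of training and then run the sessions, and the Discussion also speaks of delivery by physical education teachers.

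**What the result is said to be about.** The wording takes three forms:
- *Package.* Section 3.7.2 says the comparison is meant to "determine whether a comprehensive teaching model (TGfU) integrated with alternative sports provides incremental or superior benefits" over usual practice. The aim in section 2, to "evaluate the effectiveness of an alternative sports program in a school setting, compared to standard physical education", can be read the same way.
- *Sports.* The Introduction says "RENUÉVATE will provide robust evidence on whether alternative sports can serve as an inclusive and engaging strategy within the school setting". The Discussion foresees "supporting the incorporation of alternative sports as a valid strategy for improving physical fitness, motor skills, and enjoyment of physical activity". An earlier Discussion paragraph, on the evidence gap, and the Conclusion (section 5) also name alternative sports as the thing evaluated.
- *Teaching model.* Section 3.9.2.3 says the accelerometry controls "the physical activity dose strictly linked to the pedagogical model (TGfU vs. Traditional)".

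The Abstract adds that the design and the structured intervention "will generate robust evidence on the physical, motor, and affective-motivational mechanisms associated with this pedagogical approach".

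**The concern.** A difference between arms could come from the sports, from TGfU, from the intensity range, from the instructor, or from any mixture of these. The protocol gives its own reason to take this seriously: the Introduction says that the type of sport and the pedagogical model both influence adherence and learning. It then varies both together, and its limitations paragraph does not mention that they cannot be separated.

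The Discussion directs the findings at decisions in education and public health. If a positive result is reported as an effect of alternative sports, a school might change its sports when a change of teaching would have done as much. It might also adopt the sports without TGfU and see no gain. The wording of the conclusion therefore affects what readers will do with the trial.

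**Working it through.** The plan gives no figure for this point. The sample size in section 3.2 plays no part in it and reproduces within rounding: 44 per arm, design effect 1 + (35 − 1) × 0.03 = 2.02, 44 × 2.02 = 88.88 (stated as about 88), and 88 / 0.85 = 103.5, so 104.

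**Step 1: set the arms side by side.**

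| Component | Intervention | Control | Section |
|---|---|---|---|
| Sports | Four alternative sports | Basketball, soccer, handball | 3.7.1, 3.7.2 |
| Teaching | TGfU | Mainly command style | 3.7.1, 3.7.2 |
| Intensity range | Prescribed for each phase | None stated | 3.7.3, 3.7.2 |
| Instructor | External, trained (but see 3.8 and 4) | Regular teacher | 3.3, 3.7.1 |
| Frequency and duration | Equalised | Equalised | 3.7.2 |

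**Step 2: what can be estimated.** There are 3 schools with 2 classes each, so 6 classes. A class-level model with three school indicators and one arm indicator has 4 columns and rank 4: the arm effect is estimable. Replace the arm indicator by separate indicators for sport, teaching, intensity and instructor. The model now has 3 + 4 = 7 columns, but the four component columns are identical, so the rank stays at 4. If the instructor did not differ, there would be 3 + 3 = 6 columns, and the rank would again be 4. More pupils or more classes on the same plan would not change this.

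**Step 3: what the arm effect contains.** Four two-level components define 2⁴ = 16 combinations, of which 2 are observed. The expected difference between arms is the sum of 4 main effects and 16 − 1 − 4 = 11 interaction terms: one equation for 15 unknowns. Suppose, as an assumption, that all main effects are non-negative and there are no interactions. The share due to the sports could then be anything from none to all of the observed difference.

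**Step 4: compare the wording with the contrast.** The package wording in section 3.7.2 matches what Step 2 shows to be estimable, although it does not name the intensity range or the instructor. The sports-only wording in sections 1, 4 and 5 and the teaching-only wording in section 3.9.2.3 each assign the single arm effect to one component. They also disagree with each other.

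**Step 5: mechanisms.** In-class activity is recorded by accelerometer in each class over the 8 weeks (section 3.9.2.3), and heart rate in a 25% subsample (section 3.7.3.2). These can describe the activity dose during the intervention. No listed measure can divide a benefit between sport and teaching.

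**The case against.** The strongest defence is that comparing a multi-component programme with usual practice is legitimate, and that the protocol declares it. The Abstract says the sports are taught by TGfU. The hypothesis is stated for participants assigned to the intervention, the aim speaks of a programme, and section 3.7.2 defines the package explicitly. The sentence quoted from the Introduction claims no effect independent of the teaching method, and the policy statement in the Discussion is conditional on the intervention being effective. The intensity range belongs to the programme, and in-class activity is measured.

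Most of this stands, and it limits the point in three ways.
- A reader might infer that the trial cannot support its stated conclusions at all. The documents do not support that: the package question is identified, and the background statement in the Abstract and the aim in section 2 are compatible with it.
- A reader might infer that every candidate mediator is measured only together with the outcomes, so that nothing can be learned about process. That is not so, because activity is recorded in class throughout the 8 weeks.
- The intensity range is part of the package and not a separate design flaw.

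The defence does not explain why section 3.9.2.3 ties the activity contrast to the teaching model alone while sections 4 and 5 name the sports. Nor can this be put down to shorthand throughout: the Discussion traces the expected affective and motor gains to features of the sports themselves.

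**Conclusion.** The concern holds as a mismatch between the contrast and the claims. The trial can estimate the effect of the whole package against usual physical education. It cannot assign a difference to the sports, as the Introduction, Discussion and Conclusion are worded, or to the teaching model, as section 3.9.2.3 is worded. The share due to any one component is not estimable at any sample size.

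This rests on the arms being delivered as described, with no class receiving a mixed combination. The instructor difference depends on sections 3.3 and 3.7.1, which conflict with section 3.8 and the Discussion. If it disappears, the other three components remain inseparable. No analysis or sample-size figure is affected, but what the trial may conclude is, so the text should be corrected.

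**What to change.** 1. In the Introduction (the sentence on what the trial will show), section 3.9.2.3, the Discussion (the paragraphs on the evidence gap and on decision-making) and the Conclusion, state the contrast as the RENUÉVATE package versus usual physical education. Define the package as alternative sports taught by TGfU, at the set intensity, by the study's instructor.
2. Add to the limitations in the Discussion that separate effects of sport content, teaching model, intensity and instructor cannot be identified and will not be claimed.
3. Reconcile sections 3.3 and 3.7.1 with section 3.8 and the Discussion on who delivers the intervention sessions, so that the package is defined once.
4. In the Abstract, limit the promise about mechanisms to a description of outcomes and in-class activity dose. The background statement in the Abstract and section 2 need at most a clarifying phrase.

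The cost is a narrower conclusion. Arms, sample size and measurements stay as they are. A claim about the sports alone would need a comparator sharing the teaching model, instructor and intensity; this point does not ask for one.
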